## Abstract

**Background:**

Non-arthritic hip disorders are defined as abnormalities of the articulating surfaces of the acetabulum and femur before the onset of osteoarthritis, including intra-articular structures such as the acetabular labrum and chondral surfaces. Abnormal femoroacetabular morphology is commonly seen in young men who constitute much of the UK military population. Residential multidisciplinary team (MDT) rehabilitation for patients with musculoskeletal injuries has a long tradition in the UK military, however, there are no studies presenting empirical data on the efficacy of a residential MDT approach compared with individualised conventional outpatient treatment. With no available data, the sustainability of this care pathway has been questioned. The purpose of this randomised controlled trial is to compare the effects of a residential multidisciplinary intervention, to usual outpatient care, on the clinical outcomes of young active adults undergoing treatment for non-arthritic intra-articular hip pain.

**Methods/design:**

The trial will be conducted at the Defence Medical Rehabilitation Centre, Headley Court, UK. One hundred military male participants with clinical indicators of non-arthritic intra-articular hip pain will be randomly allocated to either: (1) 7-day residential multidisciplinary team intervention, *n* = 50; (2) 6-week physiotherapist-led outpatient intervention (conventional care), *n* = 50. Measurements will be taken at baseline, post-treatment (1-week MDT group; 6-weeks physiotherapy group), and 12-weeks. The primary outcome measures are the function in daily living sub-scale of the Copenhagen Hip and Groin Outcome Score (HAGOS), the physical function subscale of the Non-arthritic Hip Score (NAHS), and VAS pain scale. Secondary outcomes include objective measures of physical capacity and general health. An intention-to-treat analysis will be performed using linear and mixed models.

**Discussion:**

This study will be the first to assess the efficacy of intensive MDT rehabilitation, versus conventional outpatient care, for the management of non-arthritic hip pain. The results from this study will add to the evidence-base and inform clinical practice for the management of intra-articular non-arthritic hip pain and femoroacetabular impingement in young active adults.

**Trial registration:**

ISRCTN Reference: ISRCTN 59255714 dated 11-Nov-2015

**Electronic supplementary material:**

The online version of this article (doi:10.1186/s12891-016-1309-z) contains supplementary material, which is available to authorized users.

## Background

Hip and groin pain in adults have been traditionally attributed to osteoarthritis (OA), however, advancements in imaging and arthroscopy have improved health care providers’ understanding of hip disorders that occur before the onset of arthritis [1]. Non-arthritic hip disorders are defined as abnormalities of the articulating surfaces of the acetabulum and femur before the onset of osteoarthritis, including intra-articular structures such as the acetabular labrum and chondral surfaces [2, 3]. Abnormalities of these structures can lead to a continuum of biomechanical changes and extra-articular adaptations that can cause significant hip pain and dysfunction in young adults [3, 4].

Femoroacetabular impingement (FAI) is a common cause of hip symptoms and impaired functional performance in younger active populations [5]. FAI is a mechanical disorder characterised by repetitive contact between the acetabulum and proximal femur, potentially resulting in damage to the hip joint cartilage and labrum [6]. FAI comprises several hip-shape abnormalities, including CAM and pincer morphology, and has been suggested as a risk factor for hip OA [7]. However, the link between FAI and development of hip OA is unclear. Whilst CAM-type FAI has been shown to be strongly associated with fast-progression to end-stage OA [8], the same association has not been demonstrated for pincer-type FAI and early OA [9]. Therefore, whilst intuitively appealing to conclude FAI structural changes lead to joint damage and development of early OA, a causal link remains unproven [10].

### Conservative management of intra-articular hip disorders

To date, patient outcomes after treatment of intra-articular hip disorders have been limited to post-surgical outcomes [11, 12]. Consequently, comprehensive treatment outside of surgery remains ill-defined [1]. Although the success of conservative management for non-arthritic, intra-articular hip pain is inconclusive [10], positive results have been reported in two recent publications [1, 13]. Hunt et al. [1] and Emara et al. [13] reported outcomes of conservative care for patients with clinical indicators of non-arthritic, intra-articular hip pain. Both studies demonstrated significant improvements in pain and physical function from baseline to +1-year follow-up. The observational nature of these studies prevent speculation on the mechanisms underpinning the effectiveness of conservative treatment, however, these are important findings as many experts had previously concluded there was no role for conservative treatment [10].

A recent systematic review found the experimental evidence reporting non-operative treatment for FAI is limited to 5 articles providing a low-level of evidence [10]. Whilst limited the experimental evidence promotes physical therapy led care for FAI. Fundamental to all regimens is an exercise-based programme focused on the core hip musculature, individually tailored strengthening exercises, manual therapy, home-based exercise and education. In addition, the early use of simple analgesia and NSAIDs is promoted. Whilst there is a suggestion that this form of physical therapy and education confer some benefit to patients, the literature is not supported by any randomised controlled trials, and conservative treatment regimens need to be evaluated more extensively and rigorously to determine the true clinical effectiveness [1, 5, 10, 13].

### Structure and process of hip pain rehabilitation in the UK military

Abnormal femoroacetabular morphology is commonly seen in young men comprising much of the UK military population [14]. Residential multidisciplinary team (MDT) rehabilitation for patients with musculoskeletal injuries has a long tradition in the UK military. Rehabilitation most often takes place in two clinical settings; out-patient primary care rehabilitation facilities (PCRF), and specialist in-patient residential centres. Rehabilitation at the PCRF is focussed primarily on physical function led by a physiotherapist, whereas residential centres have access to larger consultant led multidisciplinary teams delivering a broader psychosocial approach to treatment. However, whilst single treatment entities for hip conditions have been the subject of evidence-based examination, there has been little evaluation of group-based MDT management programmes combining single treatments. Aprile et al. [15], showed no statistically significant difference between outpatient/individual versus inpatient/group hip rehabilitation for any validated clinical outcome measure. Angst et al. [16] found comprehensive inpatient team rehabilitation led to statistically and clinically important improvements in pain and function for patients with co-morbid hip pain. However, there are no studies presenting empirical data on the structure and process of non-arthritic hip pain care for a young active military cohort, or whether a broader residential MDT approach provides better care than individualised conventional outpatient treatment.

With no available data, the effectiveness of MDT residential care remains unclear. Therefore, the purpose of this study is to compare the effects of a residential, multidisciplinary intervention, to usual outpatient care, on the clinical outcomes of UK military patients undergoing treatment for non-arthritic intra-articular hip pain. This protocol describes the design and analysis plan for a randomised controlled trial.

## Methods/design

### Study aims and hypothesis

The primary aim of this study is to compare the effects of a 7-day residential multidisciplinary intervention, to usual outpatient care, on pain and physical function in military patients with non-arthritic intra-articular hip pain.

The secondary aims are to assess changes in relevant musculoskeletal variables of treatment including hip range of motion (HROM), walking ability, and postural control during single leg stance. The primary time point is measured at 3-months (12-weeks).

### Primary hypothesis

No studies have compared the effects of MDT residential rehabilitation interventions versus conventional outpatient care for non-arthritic hip pain. However, systematic reviews and RCT’s provide evidence that MDT inpatient rehabilitation programmes are more effective than usual care (moderate evidence) to improve pain, well-being and self-reported function in heterogeneous patient groups with musculoskeletal conditions [17–20]. Therefore, we will test the following primary hypothesis:i.A 7-day multidisciplinary residential intervention will result in greater improvements in treatment outcomes compared to individualised outpatient treatment in young adults with non-arthritic hip pain.

### Secondary hypotheses

There is evidence from RCT’s showing that a greater number of therapist contacts and higher intensity rehabilitation improves rehabilitation outcomes in patients with musculoskeletal pathology [21, 22]. This suggests a dose-response for treatment/training outcomes [23]. Class-based supervised exercise rehabilitation has also been shown to improve health outcomes compared to a non-supervised home-based group [24]. In our study a residential rehabilitation group will receive a period of intensive, supervised class-based treatment. An outpatient group will undergo a series of regular clinic appointments combined with unsupervised home-based exercise. We will test the following secondary hypothesis:ii.In patients with non-arthritic hip pain, residential MDT treatment, compared to outpatient physiotherapist led care, will result in a significant:Improvement in hip muscle strength (as measured by hand-held dynamometry)Increase in hip range-of-motion (as measured by inclinometer)Improvement in health related quality-of-life (as determined by the EuroQuol-5D)Greater adherence to home-based exercise (as determined by patient self-report diary)

### Design

The study is a superiority parallel-group, randomised controlled trial (RCT) of a 7-day residential, multidisciplinary intervention (MTD programme), and individualised physiotherapy outpatient care (IP programme) with 3-month follow-up. Measurements will be taken at baseline, post-treatment (7-day MDT; 6-weeks IP) and 12-weeks. We considered including a sham control treatment group but felt in a well-motivated young military cohort this could have a negative impact on recruitment. Trial participants, assessors and clinical/research staff will be un-blinded to treatment allocation. The protocol will conform to the CONSORT (Consolidation of Standards of Reporting Trials) guidelines for non-pharmacological interventions [25], and principles of the Declaration of Helsinki [26].

### Setting

The study will be conducted at a specialist UK military rehabilitation centre.

### Ethics

The study has been reviewed and approved by the UK Ministry of Defence (MOD) research ethics committee (study reference protocol 576 dated 01 Nov 2014). Any requirement for protocol modifications will be submitted for authorisation to the MOD research ethics committee.

### Participants

We will recruit 100 male participants aged 18 to 50 years attending the Centre for Lower Limb Rehabilitation injury assessment clinic (Defence Medical Rehabilitation Centre (DMRC), Headley Court, UK) with symptoms of intra-articular non-arthritic hip pain. Eligible participants must meet the criteria detailed in Table 1.

**Table 1 Tab1:** Study eligibility criteria

Inclusion criteria	
1. Anterior or lateral hip pain for at least 3-months	
2. Clinical signs and symptoms of prearthritic intra-articular hip pathology/FAI diagnosed by a specialist Consultant Physician^a^	
3. Physical examination findings or reproduction of pain in the groin or lateral hip with the log roll, anterior hip impingement test, Thomas test or resisted straight leg-raise test^b^	
4. Sufficient time to keep therapeutic appointments	
5. Aged ≥ 18 years	
6. Male	
Exclusion criteria	
1. Inflammatory arthropathy	
2. Hip infection or tumour	
3. Hip fracture including history of stress fracture	
4. Existing extra-articular hip disorders and/or any other pre-existing hip pathology	
5. Major structural deformity of the hip	
6. Advanced degenerative disease of the hip (Tönnis classification 2–3) [27]	
7. Any physical impairment or co-morbidities (including cardio-vascular disease) precluding the safe participation in the rehabilitation programme and/or assessment procedures	
8. History of congenital/adolescent hip disease	
9. Cortico-steroid or analgesic injection intervention for hip within the previous 30-days	
10. Clinical signs of lumbar spine disease including radiculopathy	
11. Insufficient capacity to provide informed consent	
12. Aged ≥ 50 years	
13. Female	

^a^Consultant diagnostic criteria will include [1] anterior or lateral hip pain for a minimum of 3-months; [2] history of pain worsening with activity, pivoting, hip flexion or weight bearing; [3] pain associated mechanical symptoms including popping, clicking or locking; [4] pain at rest; [5] physical examination findings or reproduction of pain in the groin or lateral hip with the anterior hip impingement test; [6] physical examination findings that exclude the spine and other lower-limb disorders as a potential source of pain and dysfunction; [7] patient self-report of sensations of instability during functional movements (e.g., squatting)

^b^Measurement techniques and positions are described at appendix 10 of the Additional file 1

### Procedure

The procedure and flow of participants is outlined in Fig. 1. Patients with symptoms of hip pain will undergo preliminary screening conducted by their local unit medical officer. The only screening criteria used at this initial stage is the patient reporting symptoms of hip/groin pain for at least 3-months. Potential participants will then attend a multidisciplinary injury assessment clinic (MIAC) at DMRC for a comprehensive musculoskeletal examination by a specialist rehabilitation consultant, and experienced musculoskeletal physiotherapist. The purpose of the MIAC is to establish the patient’s eligibility for inclusion in the study. Because attendance at the MIAC is directly linked to this study, patient consent to attend the MIAC will be sought in advance via postal consent forms and a patient information sheet, and follow-up telephone calls from study administrators where necessary. The information sheet will detail the nature of the study and will include confirmation that consenting eligible participants will be randomly assigned to one of the following two treatment groups:

**Fig. 1 Fig1:**
[figure not shown]
Participant flow through the study. DMRC = Defence Medical Rehabilitation Centre; IP = individualised (outpatient) programme; MDT = multidisciplinary team (residential); MIAC = multidisciplinary injury assessment clinic

i.
**Group 1- MDT residential intervention**. Participants will receive an intensive, 7-day residential (in-patient) intervention at DMRC Headley Court. The intervention will include group-based exercise, manual therapy, hydrotherapy and education. The intervention will be delivered by a multidisciplinary team comprising a consultant physician, physiotherapist (PT), occupational therapist (OT) and exercise rehabilitation instructor (ERI). The intervention is anchored by admission and discharge procedures at day one and day seven respectively. Participants will typically complete seven therapy sessions each day of 30–60 mins duration over the remaining 5 days. The sessions enhance social contacts through group-based feedback before and after treatment, and by promoting partner and group exercise [27].ii.
**Group 2- IP outpatient intervention**. Participants will receive 8 treatment sessions, delivered over 6-weeks, combined with a home-based exercise programme. The first and last treatment session will be 45–60 min in duration. The remainder will be 30 min. The intervention will include individualised exercise, manual therapy and individually tailored education/advice. This programme will be delivered as an outpatient service from DMRC and led by an experienced physiotherapist. The treatment session duration reflects a realistic treatment dosage in clinical practice and has been shown sufficient to allow all components of treatment to be carried out [28]. Delivering the intervention in this realistic setting is important to determine the likelihood of effectiveness of the intervention in everyday practice [29]. The home-based programme will initially comprise 3-sessions per week but can be adjusted by the physiotherapist in response to patient progress. The home-based exercise programme in this study will be restricted to 3-times per week based upon the limited available evidence from clinical trials in non-arthritic hip pain [30], and a compromise between addressing the clinical goals whilst optimising adherence [31]. The home-based programme will be tailored to the individual needs of the patient, and utilise self-monitoring by means of an exercise diary.

A definition of rehabilitation based on the concepts of structure and process is frequently used when assessing the content of health care interventions [32]. In our study the therapeutic content (e.g., exercise, manual therapy, education, home-based programme) is the same for both study groups. However, the structure and process will differ significantly. The residential arm is group treatment delivered by a MDT in a residential setting over 7-days. The outpatient arm is physiotherapist led individual treatment delivered during a series of weekly appointments over 6-weeks. Therefore, the amount of direct therapist contact, hands-on physical therapy and instructions surrounding exercise adjustment and education will differ. A detailed description of the treatment methods is contained in Table 3 and Additional file 1.

Eligible patients will be invited to participate in the study and complete an informed consent form. Patients agreeing to participate will be informed of treatment group assignment and referral arrangements by a civilian member of the clinical team, and all necessary study documents will also be provided. Ineligible patients will receive an ongoing referral in accordance with the existing UK military best practice care pathway. Following consent, participants will be consecutively randomised into either the residential or outpatient group by an independent administrator not involved in recruitment, assessment or treatment of participants. Baseline testing will be conducted immediately prior to commencement of treatment. Participants will be reassessed on completion of treatment (1-week (MDT); 6-weeks (IP)), and again at 12-weeks (week 12). During the 12-week follow up period, all participants will be advised to continue with an unsupervised home exercise programme. A log book record of exercise participation will be maintained during this period, and participants will be asked to refrain from seeking other treatments during the study.

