Group exercise	Strengthening exercises, active range of motion exercises, functional balance drills, gait drills, progressive co-ordination drills, non-weight-bearing aerobic/endurance exercise, minor team games.	Restore strength of deep hip stabilisers, improve core strength, increase joint range of motion, improve balance and neuromotor control, improve muscle endurance, promote group cohesion and social support.	12 (30–45 min)
Individual physiotherapy^a^	Manual therapy techniques, muscle activation and timing patterns, active and passive range of motion exercises, advice on home-exercise, gait re-education training.	Improve quality and timing of movement, improve muscle strength, reduce pain, increase joint range of motion, induce relaxation, promote normal walking gait.	5 (30 min)
Hydrotherapy/swimming	Non weight-bearing aerobic exercise, strengthening exercises, active range of motion exercises, self-paced recreational swimming, progressive/assisted weight-bearing exercise and activity.	Improve muscle strength, improve aerobic capacity, increase joint range of motion, improve confidence in weight-bearing, induce relaxation, promote enjoyment and variety of treatment.	3 (60 min)
Individual occupational therapy^b^	Relaxation techniques, postural re-education, cognitive behavioural therapy (CBT) techniques, self-help coping strategies, pain management.	Induce relaxation, promote behavioural change, control pain, correct/improve poor posture.	3 (60 min)
Patient education	Coping with pain, benefits of exercise, joint protection, anatomy and pathology of hip pain, nutrition.	Activity modification, reduction of pain, promotes behavioural change, weight management, improve knowledge of treatment options, improve ability to relax, improve knowledge of self-help techniques.	2 (60 min)

^a^Exercise dosage, progression and intensity will be governed by the physiotherapist and tailored to the needs of each individual patient; ^b^Occupational therapy referrals will be individually prescribed to selected patients

**Table 3 Tab3:** Overview of Outpatient Individual Programme (IP Group) and Residential (MDT Group) Study Treatment Schedule

Outpatient (IP) Protocol	Residential (MDT) Programme
Session 1 (45–60 mins)^a^	Day 1
• Subjective and objective assessment (20–25 mins)	• Admission MDT clinic and baseline measures
• Patient education (5-mins)	Day 2
• 1–2 manual therapy techniques (5–10 mins)	• Group-based introduction to treatment goal 1

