### Sample size

The primary endpoint will be change from baseline to 12-weeks in (a) the HAGOS ‘physical function in daily living’ subscale and (b) VAS numeric pain rating. Sample size calculation is based on clinically relevant changes over the study period (e.g., score changes between baseline and follow-up should be, on average, subjectively perceptible by the participant). The minimum clinically important difference (MCID) in the HAGOS subscale has been suggested to be 4.8–5.2 points [53]. Between participant standard deviations have not been widely reported for the VAS using intra-articular hip pain patients [1, 10]. Therefore, the required sample using a MCID of 5.2 between groups on the HAGOS subscale and a standard deviation of 11 points, with a significance level of 0.05 (2 tailed) and a power of 80 %, is 43 per group. Allowing for an estimated drop out rate of approximately 15 % at the 12-week follow-up, a total of 100 participants will be recruited into the study. Based on current referral rates it is anticipated this sample target will be met from routine referrals to DMRC Headley Court and no additional strategies to promote enrolment are required. The sample size was calculated using G*Power software Version 3.0.10 (Franz Faul, Universitaet Kiel, Germany). There is currently no RCT reporting the effects of a residential MDT intervention versus outpatient individualised treatment approaching this sample size in the available literature.

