### Statistical analysis

The statistical analysis will be undertaken in accordance with the intention-to-treat (ITT) principle. The ITT analysis will include all participants, including those who do not fully adhere to the protocol and those with missing outcome data. A per-protocol analysis will also be performed where appropriate. Demographic and clinical characteristics as well as baseline data will be presented to assess the baseline comparability of the two groups. Differences from baseline to each time point will be calculated for all primary and secondary outcomes. Descriptive statistics will be presented for each group as mean change, standard deviations and confidence intervals (CI) for continuous variables, and frequencies and percentages for categorical variables. A longitudinal repeated measures design will be used to assess changes from baseline, and to make between group comparisons for the continuous outcome measures. Between group comparisons will be made immediately post treatment (1 week residential group; 6 weeks outpatient group) and at 12 weeks.

The effect of the interventions over time will be compared using linear and mixed models. These models are chosen as they appropriately adjust for correlation that occurs from collecting multiple observations per participant [37]. At the 1,6 and 12 week time points, continuous variables will be analysed using a mixed model repeated-measure analysis of variance (ANOVA) model (with treatment as the between group factor and time as the repeated factor). The non-parametric equivalent or data transformation will be used if non-normal distributions apply. Where significant differences occur, post-hoc comparisons will be conducted using Tukey’s multiple comparison procedure. Differences in nominal/ordinal data will be analysed using the *χ*

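### Residential participants are treated in groups and outpatients singly, but the stated model and sample size treat all participants as independent; if residential courses are shared and outcomes correlate within them, the standard error is understated

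*Protocol article*

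**What the plan says.** The Procedure section contrasts the two arms directly: "The residential arm is group treatment delivered by a MDT in a residential setting over 7-days", whereas the outpatient arm is individual treatment led by a physiotherapist. It also describes how the residential sessions are meant to work: "The sessions enhance social contacts through group-based feedback before and after treatment, and by promoting partner and group exercise". Table 2 lists 12 group exercise sessions a week, and their goals include to "promote group cohesion and social support". Table 3 adds group introductions to the treatment goals and group education topics. Allocation, under Randomisation, is of individuals in a 1:1 ratio.

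The Statistical analysis section specifies a mixed-model repeated-measures ANOVA, "with treatment as the between group factor and time as the repeated factor". It gives the reason for choosing such models: they deal with correlation among several observations on one participant. No term for residential course, group or therapist appears.

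The Sample size section works from a between-group difference, a standard deviation, a significance level, power and dropout, and arrives at 43 participants in each arm before dropout: "with a significance level of 0.05 (2 tailed) and a power of 80 %, is 43 per group". No ICC or design effect enters. The endpoint is fixed there too: "The primary endpoint will be change from baseline to 12-weeks".

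**The concern.** This is a partially nested design. Participants are randomised singly, then one arm is treated in groups and the other is not. People who spend a week exercising, receiving feedback and being taught together, by the same staff, can come out more alike than people from different weeks. That adds a variance component between courses, in the MDT arm only. A model whose only correlation is within participant leaves this component out.

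When the component is positive, the model overstates the information in the MDT arm. The confidence interval for the treatment difference is then too narrow and the test rejects too often. The trial is a superiority comparison of group residential care with individual care, so the omitted variance lies inside the contrast being tested. Once the standard error is corrected, power is also lower than planned.

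**Working it through.** **The plan's own figure.** The stated 43 per group is a calculation for independent participants. With the plan's inputs (difference 5.2, SD 11, two-sided 0.05, 80% power):

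n per group = 2 × (1.960 + 0.842)² × 11² / 5.2² = 70.2, so 71 (72 with the exact t calculation).

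The figure of 43 does not follow from those inputs. That is a separate matter and is not pursued here. The error rates below do not depend on it, because they are ratios of standard errors. The step from 43 to 100 recruited is consistent with adding 15% (43 × 1.15 = 49.5, so 50 per group).

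**Inputs for the clustering check**
- Equal arms, 50 randomised to each: Abstract and Sample size.
- Recruitment and data collection from January 2016 to December 2017: Timeline.
- Trial participants per course, m: not given. Assumed 2.4 to 10.
- ICC at 12 weeks: not given. Assumed 0.01 to 0.10.

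**What the timeline implies for m.** The period is 24 months. Allowing about 3 months for the last 12-week follow-up leaves about 21 months to enrol 50 MDT participants: 50 / 21 = 2.4 a month. With monthly courses (an assumption, since course frequency is not stated), m is about 2.4. At this rate, 6 per course would mean a course every 6 / 2.4 = 2.5 months, and 10 per course one every 4.2 months.

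**Formulas**
- MDT design effect: DE = 1 + (m − 1) × ICC. The IP arm is taken as 1.
- True over naive variance of the difference, equal arms: V = (DE + 1) / 2.
- True over naive standard error: √V.
- Actual two-sided type I error: 2 × [1 − Φ(1.96 / √V)].

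**Results**

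| m | ICC | DE | V | √V | Type I error |
|---|---|---|---|---|---|
| 2.4 | 0.01 | 1.014 | 1.007 | 1.003 | 5.1% |
| 2.4 | 0.05 | 1.070 | 1.035 | 1.017 | 5.4% |
| 2.4 | 0.10 | 1.140 | 1.070 | 1.034 | 5.8% |
| 6 | 0.05 | 1.250 | 1.125 | 1.061 | 6.5% |
| 10 | 0.10 | 1.900 | 1.450 | 1.204 | 10.4% |

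Example for m = 6 and ICC 0.05: DE = 1 + 5 × 0.05 = 1.25; V = 2.25 / 2 = 1.125; √V = 1.061; 1.96 / 1.061 = 1.848; error = 6.5%.

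**Power, with the standard error corrected.** A design with a true 80% power would have Φ[(1.960 + 0.842) / √V − 1.960]. This gives 75% at m = 6 and ICC 0.05, and 64% at m = 10 and ICC 0.10.

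**Limits of the approximation.** The formulas use equal course sizes and normal critical values. Unequal course sizes raise the design effect somewhat. Fifty MDT participants form about 21 courses at 2.4 each, 8 at 6 each and 5 at 10 each. With the smaller numbers of courses, normal critical values are themselves optimistic.

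**The case against.** A reader might infer that the MDT standard errors are certainly too small, or that the type I error is about 10%. The protocol supports neither. Understatement needs two things: several trial participants on the same course, and a positive ICC at 12 weeks. The protocol states no group size, course frequency, number of courses or ICC, and never says that trial participants are admitted together. Operational detail may be in the supplementary intervention guide, which is not shown. The 10.4% figure pairs the top of both assumed ranges, and the accrual implied by the timeline points to the lower part of the range.

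Some features would also weaken correlation within a course. The endpoint falls about 11 weeks after a 7-day stay, following an individual, unsupervised home programme. Table 2 also includes five individual physiotherapy sessions and, for selected patients, individual occupational therapy, with exercise dosage tailored to the person. These points stand, and they limit the size of the problem. They do not show that the ICC is zero, and batching of participants into fewer courses cannot be excluded.

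It can also be said that an article leaves the specification of random effects to the full analysis plan. That carries less weight here. The article names the factors in the model and says which correlation the model is meant to handle, and that correlation is within participant only.

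Finally, with few courses the course variance is poorly estimated and degrees of freedom are lost, so the remedy is not free. That stands and is counted as a cost.

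**Conclusion.** The point holds in conditional form. The protocol describes a treatment meant to make participants in one arm influence each other, then fixes a model and a sample size that treat participants as independent. If courses are shared and the 12-week ICC is above zero, the standard error of the treatment difference is understated and the two-sided error is above 5%.

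On the assumptions shown, the likely size is modest: roughly 5.1% to 6.5%. The lower end corresponds to the accrual implied by the timeline with monthly courses, and the upper end to 6 per course with ICC 0.05. The 10.4% case is an outer bound of the assumed ranges and not an expectation. This is a change worth making before analysis, but not a flaw that invalidates the trial.

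**What to change.** Record the residential course (admission date or course number) for every MDT participant. This has to be captured during data collection, because an analysis plan cannot restore it if it was never kept.

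Fit the 12-week primary model with a random intercept for course in the MDT arm only, residual variance allowed to differ by arm, and Kenward-Roger or Satterthwaite degrees of freedom. Report the estimated ICC with the number and size of courses. State an assumed ICC and course size in the sample size section, with the resulting factor (1 + DE) / 2 on the number per arm. If more than one physiotherapist delivers the IP arm, consider clustering by therapist there too; the protocol does not give the number.

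The cost is one recorded field and one model term. The confidence interval will be somewhat wider. If there are few courses, the variance component will be imprecise and degrees of freedom will be lost. If most participants attend separate courses, little will change. Treatment, recruitment and outcome measurement are unaffected.
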